#### Primary outcome measure

The trial has two coprimary outcome measures: International Consultation on Incontinence Questionnaire-Urinary Incontinence Short Form (ICIQ-UI SF)^32^ and the International Prostate Symptom Score (IPSS).^33^

These outcomes measure leakage (ICIQ-UI SF) and bladder over activity (IPSS) and were used to determine our sample size. They are validated for use in men and women.

The ICIQ-UI SF provides a brief and robust measure to assess the impact of symptoms of incontinence on QOL and outcome of treatment. It consists of four questions measuring frequency of UI, amount of leakage, overall impact of UI and when leakage occurs. It has grade A for validity, reliability and responsiveness to change established with rigour on one data set. The total score ranges from 0 to 21 with higher values indicating increased severity of symptoms.^32^

The IPSS is based on the answers to seven questions concerning urinary symptoms. The questions refer to the following urinary symptoms: (1) incomplete emptying; (2) frequency; (3) intermittency; (4) urgency; (5) weak stream; (6) straining; and (7) nocturia. Question 8 refers to the patient’s perceived QOL. Each question is assigned points from 0 to 5 indicating increasing severity of the particular symptom. The total score ranges from 0 to 35 (asymptomatic to very symptomatic). Although there are presently no standard recommendations for categorising the IPSS score, patients can be tentatively classified as follows: 0–7=mildly symptomatic; 8–19=moderately symptomatic; 20–35=severely symptomatic.^33^

#### Secondary outcome measures

Qualiveen is an eight-item self-administered urinary QOL questionnaire validated in the neurogenic populations.^34^
Parkinson’s Disease Questionnaire-8 (PDQ-8) is a validated eight-item self-administered questionnaire measuring Parkinson’s specific QOL.^35^
A 72-hour bladder diary will be completed by participants during the week postrandomisation before commencing the use of the device at home (week 0), during week 7 and week 11 and will record frequency of micturition, leakage episodes and urgency. Participants will be advised to start the diary in the morning (first void of that day) following their clinic visit.Compliance: the stimulation unit will record how often and for how long the participant has used the unit during the 6 weeks of intervention, and data will be downloaded at clinic on receipt of the unit. The units are locked so that it is not possible for the participants to change settings or delete data.Resource use questionnaire completed by the participant at 6 and 12 weeks will monitor visits to the doctor/nurse/hospital, medications bought/prescribed or non-prescribed and purchases such as pads.Participant experience and protocol fidelity will be assessed at 6 weeks in a brief exit questionnaire.

Questionnaires and bladder diaries to be completed at 6 weeks will be given to the participant at visit 1, and those at 12 weeks will be posted to participants. All will be returned to the trial office in reply-paid envelopes. Should participants request, completion of the questionnaires may be done verbally by telephone.

### Participant timeline/pathway

The steps within the trial that the participants will take are summarised in box 1.

Box 1The participant pathwayParticipant’s identified at clinic by local PIs, Parkinson’s nurses or research nurses.

Participant information leaflet with expression of interest form attached given/sent to patient along with preaddressed envelope.

Posters also to be put up in relevant clinics to inform patients.Potential participants opt in either by phoning the trial office or by returning the expression of interest form to them.

Staff at the trial office contact participant discuss further the implications of the study and complete screening log. If willing and eligible to be a participant, then the patient is allocated a participant study number and is given an appointment to attend the clinic or for the research nurse to visit them at home (confirmed by trial office with clinic)

At the clinic/home, the participant will be consented, the clinical assessment form will be completed, randomisation will be completed (using the web-based system) and then the participant will be shown how to use the stimulation/placebo stimulation and provided with written instructions.

The participant is given a pack to take home with them containing the 3-day bladder frequency diary (with simple instructions) and the questionnaire booklet. The participant is asked to complete the bladder frequency diary during the next 3 days (starting with the first morning void) before starting to use the stimulation. The pack also contains the bladder diary and a questionnaire booklet to be completed at 6 weeks. Prepaid addressed envelopes will be available.

During the 3 days at home, the research office telephones the participant to support completion of their bladder diary. The participant either completes the questionnaires themselves or over the telephone. These diaries are then posted to the research office. Date when the participant will start using the intervention agreed and the times of the weekly follow-up telephone calls agreed.

Trial office staff will telephone the participant weekly to see how things are going, ask about change in medications, adverse events and so on and will be available for any queries. Trial office will remind/help participant to complete the diary and questionnaires at the end of 6 weeks and will get the participant to unlock the compliance monitor before sending the unit back in the prepaid Jiffy bag.

Trial office staff will post all the 12-week outcome questionnaires to the participant and telephone them to help with completion/complete over the phone depending on the participant’s preferences.

### Sample size calculation

A sample size of 208 participants randomised equally to the two arms will provide 90% power to detect a clinically important difference of 2.52 points^36^ on the primary outcome (ICIQ-UI-SF total score) at 6 weeks postrandomisation, using an independent samples t-test (two-sided significance level of 5%), based on an SD of 5 (equating to a standardised effect size of 0.5) and an attrition rate of 20% at 6 weeks. The SD of 5 is based on a recent systematic review of TTNS for OAB,^37^ where two trials reported ICIQ-UI-SF as an outcome measure, both with an SD of 4.3.^25 38^

For the coprimary outcome measure, the IPSS, the minimum clinically important difference is estimated to be 3 points^33 39^ and the systematic review of TTNS identified a single trial reporting IPSS, where the SD was 4.^40^ However, given the limited evidence available, we conservatively assume an SD of 6 points, which equates to a standardised effect size of 0.5. Therefore, a sample size of 208 will also provide 90% power to detect a clinically important difference in the IPSS.

## Recruitment

The research team at each study centre will be responsible for identifying potential participants and patients can self-refer in response to adverts by Parkinson’s UK and contact via patient research registers. Following the receipt of an expression of interest, a member of the research team will contact the patient by telephone to provide further information, assess eligibility and forward contact details to the relevant site.

### Assignment of interventions: allocation

#### Sequence generation

Participants who provide written informed consent will be randomised using a computer generated system to either TTNS intervention or non-active stimulation arm and will be minimised on two factors: (1) severity of urinary symptoms, as reported at study baseline by the IPSS in the Clinical Assessment Form, that is, mild, moderate or severe; and (2) status on antimuscarinic medication, that is, treatment naïve, failed or continuing such treatment.

#### Concealment mechanism

A web-based randomisation system will be used.

#### Implementation

Implementation will be by staff at the Centre for Healthcare Randomised Controlled trials Clinical Trials Unit (CTU) at Aberdeen.

### Assignment of interventions: blinding

#### Who will be blinded

Due to the nature of the intervention, the research team delivering the intervention will not be blinded to the treatment received; however, we have designed several different mechanisms by which participant allocation will be concealed. Participants will be blinded to group allocation. Outcome measures are primarily self-reported and submitted anonymously. Those involved in the data analyses and statistics will be blinded to the group allocation.

#### Procedure for unblinding if needed

Clinical staff are not blinded. At 6 weeks, the participant will be asked to which group they thought they had been allocated to assess the success of blinding. Data will be analysed by a statistician who is blinded to group allocation. At this stage, it they so wish, participants will be told to which group they had been assigned.

### Data collection and management

#### Plans for assessment and collection of outcomes

Data will be collected via participant-completed questionnaires at baseline and at 6 and 12 weeks. A 3-day bladder frequency diary will be completed prior to baseline, at 6 and 12 weeks. Completed outcome data are retuned by post. Relevant demographic and medical history information will be collected at baseline.

Patient resource use questionnaires will also be completed by participant at home at 6 and 12 weeks.

#### Plans to promote participant retention and complete follow-up

Nothing beyond normal encouragement to continue to use as prescribed. All participants will be offered help with setting the parameters of a stimulation unit should they purchase one.

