**Trial registration number:**

ISRCTN12437878; Pre-results.

Strengths and limitations of this studyFully powered randomised controlled study.Participants may become unblinded.Participants may want to switch arms.

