## The intervention

There is a risk of participant unblinding if the intervention or sham intervention is discussed in detail within this protocol; this will be published before trial recruitment is complete. The authors recognise the importance of the allocated intervention being accepted by the participant as the active intervention and have developed the sham intervention to be as realistic as possible yet delivering no intervention.

The treatment protocol developed by Amarenco *et al*
31 will be adopted for this trial.

All participants will use the stimulator for two 30 min sessions a week for 6 weeks. It is preferable to have 2–4 days between stimulation sessions.

A training protocol, including a manual for clinicians and instruction leaflets for participants, has been developed. Participants will be instructed to use the TTNS device twice weekly for 6 weeks with weekly telephone support by research staff.

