### Relevant concomitant care permitted or prohibited during the trial

No special provisions.

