### Provisions for post-trial care

None beyond standard care within the National Health Service (NHS). Agreed to show how to set the parameters should the participants want to buy a unit.

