### Analysis of primary outcome measures

The analysis of the coprimary outcomes (ICIQ-UI SF score and IPSS score)^32 33^ will estimate the mean difference (and 95% CIs) between the experimental and comparator arms at 12 weeks postintervention using linear mixed models adjusting for minimisation covariates (reported symptom severity and treatment category), baseline ICIQ-UI SF/IPSS score and other potentially important prognostic covariates. Recruiting centre will be included in the models as a random effect.

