### Methods to handle protocol non-adherence and missing data

The analysis will be intention to treat with no account taken of protocol non-adherence. Non-compliance to randomised allocation is not anticipated as participants are blinded throughout.

The extent of missing data will be explored in the outcomes, especially the primary outcomes. Patterns of missing data will be explored and predictors of missingness examined, especially if these vary by intervention. If necessary, multiple imputation will be used to impute missing data assuming the missingness mechanism is missing at random. A detailed statistical analysis plan will be agreed to before the end of data entry and before the treatment code is broken.

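### The offer of help with a purchased stimulator has no stated timing, so a sham participant could start active TTNS, or an active participant continue it, before the week-12 primary comparison

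*Protocol article*

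**What the plan says.** The offer is made twice. Under Plans to promote participant retention and complete follow-up: "All participants will be offered help with setting the parameters of a stimulation unit should they purchase one". Under Provisions for post-trial care: "Agreed to show how to set the parameters should the participants want to buy a unit". Neither section names a week or a condition such as return of the last questionnaires.

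On the treatment period, The intervention says "All participants will use the stimulator for two 30 min sessions a week for 6 weeks". Box 1 (participant pathway) has the unit sent back at the end of that period, and Table 2 has compliance downloaded at week 6–7.

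On the endpoint, the hypothesis is stated for 12 weeks, and Analysis of primary outcome measures compares the coprimary outcomes "between the experimental and comparator arms at 12 weeks postintervention".

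On other treatment in the meantime, Relevant concomitant care permitted or prohibited during the trial says only "No special provisions".

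On switching, the strengths and limitations list includes "Participants may want to switch arms". Methods to handle protocol non-adherence and missing data says "Non-compliance to randomised allocation is not anticipated as participants are blinded throughout", and the analysis takes no account of non-adherence.

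On disclosure, Procedure for unblinding if needed first describes asking participants at 6 weeks which group they think they were in, then says the statistician is blinded, then adds: "At this stage, it they so wish, participants will be told to which group they had been assigned".

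**The concern.** Between return of the trial unit and the week-12 outcomes there are about six weeks in which nothing in the protocol bars a participant from using a purchased stimulator. A site reading the retention section on its own could help any participant, sham included, to set one up in that interval.

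The reason given for not expecting non-compliance is that participants are blinded. Blinding does not stop someone from accepting an offer that is made to everyone. It is also less secure than the statement implies, because the disclosure sentence can be read as applying at about week 6, and a participant who learns of a sham allocation has a motive to buy a unit.

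Two things are at stake:

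- Sham participants who gain from active stimulation before week 12 shrink the intention-to-treat difference.
- Active participants who carry on with their own unit receive more than the 6-week course under evaluation.

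In either case the week-12 contrast is no longer cleanly a 6-week course of TTNS against sham, and the analysts would have little means of telling.

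**Working it through.** **Step 1. Timing, section by section**

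| Event | Timing in the protocol |
|---|---|
| Trial stimulation ends, unit returned | about week 6 (Box 1; download at week 6–7, Table 2) |
| Help with a purchased unit | no week; under retention in one section, under post-trial care in another |
| Disclosure of allocation on request | unclear: follows both the 6-week question and the sentence on analysis |
| Restriction on concomitant care | none |
| Primary comparison | 12 weeks |

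The two headings point to different timings for one offer, and no other section settles it. The window exists only if the primary endpoint is later than week 6. The hypothesis, the abstract and the primary analysis section all give 12 weeks. The Sample size calculation is worded for 6 weeks. Read literally, 12 weeks after the intervention would lengthen the window. I take week 12 of Table 2.

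**Step 2. Would such use be seen?**

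Device compliance is downloaded once, at week 6–7. The week-12 resource questionnaire covers medications and purchases such as pads, so it might catch the purchase of a unit. No described item asks whether, or when, stimulation was used.

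**Step 3. Reproduce the planned sample size**

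Inputs from Sample size calculation: difference δ = 2.52, SD = 5, two-sided alpha 5%, power 90%, attrition 20%. (The abstract gives an SD of 4.7; I use the section that shows the derivation.)

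n per arm = 2 × (1.960 + 1.282)² × SD² / δ² = 2 × 10.51 × 25 / 6.35 = 82.7, so 83. Then 83 / 0.8 = 103.75, so 104 per arm and 208 in total, as stated.

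For IPSS (δ = 3, SD = 6) the same formula gives 85 per arm, and 107 per arm (214) after attrition, within 3% of 208. Neither figure contains an allowance for crossover.

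**Step 4. Illustrative dilution**

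Assumptions, none of them from the protocol: a share c of the sham arm crosses over, crossovers gain the full effect, nobody in the active arm buys a unit, and the inputs stated for 6 weeks apply at week 12. Analysed per arm: 208 × 0.8 / 2 = 83.2.

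- Diluted difference = δ × (1 − c)
- Standard error = SD × √(2 / 83.2) = 5 × 0.155 = 0.775
- Power = Φ(diluted difference / 0.775 − 1.960)

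For c = 10%: 2.52 × 0.90 = 2.27; 2.268 / 0.775 − 1.960 = 0.97; Φ(0.97) = 0.83.

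| Sham crossover c | ICIQ-UI SF difference | Power, ICIQ-UI SF | Power, IPSS |
|---|---|---|---|
| 0% | 2.52 | 90.2% | 89.7% |
| 5% | 2.39 | 87.0% | 86.5% |
| 10% | 2.27 | 83.3% | 82.7% |
| 20% | 2.02 | 73.9% | 73.2% |

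The t-test version is lower by about half a point or less (ICIQ-UI SF: 89.8%, 86.7%, 82.9%, 73.4%).

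**Step 5. Partial effect**

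If crossovers gain half the effect, the difference becomes δ × (1 − c/2). Then 10% crossover gives the 5% row (about 87%) and 20% gives the 10% row (about 83%).

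**The case against.** The strongest reply is that the post-trial heading already supplies the timing. Participation runs to week 12, and an offer placed under complete follow-up fits help given once follow-up is complete. Read together, the two sections may mean just that. This is a fair reading and probably the intended one, but it has to be inferred. The retention section does not refer to the other, and a site acting on it alone would breach nothing.

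A second reply is that the route is demanding. A participant must buy a device privately, obtain the help and use it in time. The evaluated course is 12 sessions over 6 weeks. A unit set up at week 7 and used twice weekly gives at most (12 − 7) × 2 = 10 sessions by week 12. This stands, and it makes full effect an upper assumption.

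Third, the calculation covers only sham crossover, while extra use in the active arm could widen the difference. This also stands, so the net direction cannot be claimed.

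Fourth, handling of post-treatment use is often left to the analysis plan, which is not shown. That holds for any supplementary analysis. It does not hold for the timing of the offer, which is trial conduct, and the article describes itself as the full protocol.

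A reader might also infer that seeing the active settings would unblind participants by comparison with the trial unit. The documents do not support this: the units are locked and returned, and the sham details are deliberately withheld.

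**Conclusion.** The point holds as an unreconciled timing that leaves the week-12 comparison open to contamination which the plan neither prevents nor asks about. It should be corrected.

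A reader might go further and infer that the protocol plainly sends sham participants to active treatment before the endpoint, or that it rules crossover out. Neither is supported. One of the two statements of the offer sits under post-trial care, so the timing conflicts rather than being clearly open. The protocol says non-compliance is not anticipated, which is weaker than excluding it, and it openly lists wanting to switch arms as a limitation. What fails is the reason given: blinding does not cover an offer made to all, and it may not last to week 12 if allocation can be disclosed at about week 6.

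The size is unknown because the protocol gives no crossover rate. The power losses in the table are illustrations that rest on the four assumptions listed there; the 73–74% figure in particular is not a forecast.

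**What to change.** 1. Reconcile the retention and post-trial care sections so that both state the offer as post-trial, meaning after the participant's week-12 outcomes have been returned. State the timing of disclosure of allocation in the unblinding section so that it is consistent with this.
2. Add one item to the week-12 questionnaire: was any tibial nerve stimulation used after the trial unit was returned and, if so, when?
3. Amend the non-adherence statement so that it no longer relies on blinding alone and says that such use will be reported by arm. A supplementary analysis accounting for it is optional and may belong in the analysis plan. Intention to treat stays the main analysis.

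The cost is a few sentences, one extra question, and a wait of about six weeks for participants who want help with a private purchase. The planned sample size need not change.

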### Data management

All trial participants are given a unique identifying trial number that will be used on all case report forms for that participant. Data will be entered into the secure trial database by the data coordinator based at the STARTUP central office at Glasgow Caledonian University.

#### Confidentiality

All investigators and study centre staff involved with this trial will comply with the requirements of the General Data Protection Regulations and the Data Protection Act 2018 in regards to the collection, storage, processing and disclosure of personal information.

Data collected during the course of the research is kept strictly confidential and accessed only by members of the trial team and may be looked at by individuals from the sponsor organisation or NHS sites where it is relevant to the participant taking part in this trial.

#### Plans for collection, laboratory evaluation and storage of biological specimens for genetic or molecular analysis in this trial/future use

None.

### Access to data

All data requests should be submitted to the corresponding author for consideration. Access to anonymised data may be granted following review.

## Analysis

All analyses will be clearly predefined, in agreed statistical and economic analysis plans, to avoid bias. Following data lock, analyses will be undertaken before unblinding of group allocation takes place. Analyses will be conducted according to the intention-to-treat principle, whereby all participants with follow-up data will be analysed according to their randomised allocation. A single main analysis will be performed at the end of the trial when all follow-up has been completed.

### Analysis of primary outcome measures

The analysis of the coprimary outcomes (ICIQ-UI SF score and IPSS score)^32 33^ will estimate the mean difference (and 95% CIs) between the experimental and comparator arms at 12 weeks postintervention using linear mixed models adjusting for minimisation covariates (reported symptom severity and treatment category), baseline ICIQ-UI SF/IPSS score and other potentially important prognostic covariates. Recruiting centre will be included in the models as a random effect.

